## Abstract

Supplemental Digital Content is available in the text

## Introduction

1

Acute respiratory distress syndrome (ARDS) is a common clinical disease characterized by acute hypoxemia, decreased lung compliance, and non-cardiogenic pulmonary edema, which can cause a series of serious complications and even progress to multiple organ failure.^[1–4]^ ARDS can be attributed to a variety of factors, including sepsis, multiple injuries, massive blood transfusions, pneumonia, aspiration, and lung contusions, among others. The primary pathophysiological feature of ARDS is the accumulation of a large amount of protein-rich fluid in the alveolar space due to damage of the diffuse alveolar capillary barrier.^[5–7]^ Although comprehensive studies have provided clinicians with a better understanding of the complex pathogenesis of ARDS, the incidence rate is still increasing.^[8,9]^ There is evidence that the mortality rate of ARDS patients is as high as 30% to 40% and is therefore an important cause of death in critically ill patients.^[10–15]^ Despite more than 50 years of research, there is still no specific treatment designated for ARDS, with options limited to supportive care, including protective mechanical ventilation and restriction of fluids,^[16]^ Therefore, finding more effective prevention and treatment strategies for ARDS is an urgent concern.

Traditional Chinese medicine (TCM) characteristically takes a holistic view and differentiates syndromes and treatments, potentially offering advantages and supportive effects in the management of ARDS. There is no record of a disease called ARDS in TCM. However, according to the patients’ clinical symptoms, such as shortness of breath, high fever, dry stools, crimson tongue, and the number of pulse slips, it would be diagnosed as “asthma syndrome.” The syndrome can be subdivided into “asthma syndrome” (early) and “asthma syndrome” (late). The prescriptions determined through syndrome differentiation and treatment has played a role in the diagnosis and treatment of ARDS, laying a foundation for Chinese medicine to participate in its treatment. Chinese medicine has a wide range of mechanisms to treat ARDS, mainly by regulating the cytokine network; protecting endothelial function; through antioxidation; regulating the coagulation/fibrinolysis system, immunity, and water; and through sodium transport.^[17]^

In a previous small sample study, we found that Jiawei qianyang dan (JWQYD) can reduce the extravascular lung water index and improve the prognosis of patients with ARDS, with good clinical effect.^[18]^ It is composed of aconite, Amomum, tortoise shell, ginger, licorice, and ephedra. The protective ventilation strategy adopted in the clinic for ARDS has a high risk for mechanical ventilation that can cause lung injury (VILI). In addition, VILI also releases epithelial cytokines from nonuniform lung tissue, which further aggravates lung injury and stimulates an inflammatory response.^[19,20]^ TCM can play an supportive role in ARDS treatment. Our previous study found that the JWQYD can inhibit the release of inflammatory factors in patients with ARDS; however, there is insufficient evidence to show its clinical efficacy in patients with ARDS. Therefore, a multicenter, randomized, double-blind, placebo-controlled trial should be designed to evaluate the effectiveness of JWQYD in patients with ARDS. The experimental results will provide evidence to show that JWQYD is an effective prescription for ARDS.

## Method and design

2

### Design

2.1

This study is a prospective, multicenter, double-blind, randomized, placebo-controlled clinical trial. The center of research participation includes 4 medical institutions in China: The Affiliated Hospital of Chengdu University of TCM, The Meishan Hospital of TCM, The Neijiang Second People's Hospital, and The ICU of Suining Hospital of TCM.

The trial has been registered in the China Clinical Trial Registration Center (No. ChiCTR1900022693, which was submitted on April 23, 2019, Version.V1.4). After obtaining written informed consent, the 110 participants will be randomly divided into 2 groups at a proportion of 1:1. The 2 groups will be the integrated traditional Chinese and Western medicine treatment group and the Western medicine alone treatment group. The 2 groups of patients will receive 2 weeks of intervention treatment and 1 year of follow-up. The purpose of this experiment is to study the clinical effect of integrated traditional Chinese and Western medicine on patients with ARDS, and to evaluate the efficacy and safety of the JWQYD. At the same time, we will evaluate the long-term effect of adjuvant therapy with Chinese medicine and determine clinically effective treatments for ARDS patients. This study will follow the 2013 Standard Protocol Items: Recommendations for Interventional Trials (SPIRIT). Refer to Figure 1 for information about SPIRIT registration, intervention, and evaluation and Document 1 for the SPIRIT list.^[21]^ The study flow chart is shown in Figure 2.

**Figure 1 F1:**
[figure not shown]
Spirit figure of enrollment, interventions, and assessments. Liver function index monitoring includes:ALP, ALT, AST, GGT, Tbil, Renal function monitoring includes:BUN, Scr, eGFR. ALP = alkaline phosphatase, ALT = alanine aminotransferase, AST = aspartate transferase, BUN = blood urea nitrogen, Scr = serum creatinine, Tbil = total bilirubin, TCM = traditional Chinese medicine, GGT = γ-glutamyl-transferase, eGFR = estimated glomerular filtration rate, PɑO2/FiO2 = oxygenation index.

**Figure 2 F2:**
[figure not shown]
Flow chart of the study design. ARDS = acute respiratory distress syndrome, JWQYD = Jiawei qianyang dan.

### Moral certification

2.2

This study abides by the Declaration of Helsinki (Edinburgh, 2000). The final revised draft and informed consent have been reviewed and approved by the Sichuan Regional Ethics Review Committee of The TCM/Medical Ethics Committee of The Affiliated Hospital of Chengdu University of TCM (No.2018-KL070). If any amendments are made to the agreement, the review and approval of the ethics committee will be sought again.

### Recruitment

2.3

Participants will be recruited by doctors from the Affiliated Hospital of Chengdu University of TCM, The Meishan Hospital of TCM, The Neijiang Second People's Hospital, and the ICU of Suining Hospital of TCM. Prior to the start of the study, participants will be provided detailed information about the clinical study, including the purpose, treatment measures, schedule, and possible risks and benefits and participants or their families will be required to provide written informed consent.

### Sample size

2.4

Calculating the sample size was based on the effective rate. According to previous research, the effective rate for the treatment group with integrated traditional Chinese and Western medicine is 65.2%, and effective rate for the group with Western medicine alone is 34.8%. The software Power Analysis and Sample Size version 11.0 (PASS 11.0)was used to calculate the sample size of the 2 groups, assuming that 10% of patients are likely to be lost during follow-up, a total of 110 patients will be enrolled.

### Randomization and assignment blinding

2.5

Members of The Sichuan TCM Evidence-Based Medicine Center will use SAS 9.2 software (SAS, Cary, NC) to generate 110 random serial numbers. After screening and baseline evaluation, the patients with ARDS will be randomly divided into 1 of the 2 groups. Eligible patients will be assigned to the integrated traditional Chinese and Western medicine treatment group or the Western medicine alone treatment group at a proportion of 1:1. The group number will be provided in a carbon-free sealed envelope. The envelope will be kept by the study administrator, who will not be directly involved in any participant's recruitment or follow-up, and the group number will be disclosed later. The administrator will open an envelope and provide participants with their group number on the day of inclusion.

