### Diagnostic criteria

2.7

Participants must meet the Western medicine standard of ARDS diagnosis (Table 1),^[22]^ and the TCM syndrome judgement standard of asthma (Table 2).^[23]^ The determination of syndrome differentiation and treatment in each research center should be independently determined by 2 designated deputy chief TCM physicians.

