### Statistical analyses

3.7

Before analysis, 2 similar participants with complete data will be carefully examined to ensure that the data is correct. All data analyses will then be based on treatment intention.

The data will be analyzed using the statistical software package SPSS 22.0 (Chicago, IL). The analysis method will be selected according to the distribution characteristics of the data. The measured data will be expressed as the mean ± the standard deviation. First, the normal test and the homogeneity test of variance will be performed. In the case of normal distribution and equal variance, a *t*-test will be performed; otherwise, a nonparametric test will be utilized. The difference will be statistically significant when *P* ≤ .05.

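### The randomisation is described as one trial-wide set of 110 numbers with no stratification by the four centres, and the named tests ignore centre: a small, cheaply avoidable loss of precision

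*Protocol article*

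**What the plan says.** Section 2.1 of the protocol article says "The center of research participation includes 4 medical institutions in China" and that "the 110 participants will be randomly divided into 2 groups at a proportion of 1:1". Section 2.5 sets out the allocation in some detail. An evidence-based medicine centre uses SAS 9.2 to "generate 110 random serial numbers", the ratio is 1:1, and group numbers sit in sealed envelopes held by one study administrator, who opens an envelope on the day of inclusion. The section names no stratification factor, no block and no per-centre series.

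Section 2.7 has part of eligibility judged locally: "The determination of syndrome differentiation and treatment in each research center should be independently determined by 2 designated deputy chief TCM physicians". Section 3.7 compares measured data by a t-test or, where its assumptions fail, a nonparametric test. It names no centre term, and no separate test for rates.

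**The concern.** A single list balances the arms over the whole trial at best. Within a hospital of some 27 patients the split is left to chance. If response differs between hospitals, for whatever reason, an uneven split moves the observed arm difference in a way that balanced allocation would prevent. A test that ignores centre also leaves the between-centre variation in its error term. What is at stake is precision, and how readily a reader trusts a result when one centre is visibly lopsided. Allocation cannot be repaired once enrolment has begun, so the matter has to be settled beforehand.

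**Working it through.** **Inputs from the article.** N = 110, 1:1, four centres. Section 2.4 states that "the effective rate for the treatment group with integrated traditional Chinese and Western medicine is 65.2"% and the "effective rate for the group with Western medicine alone is 34.8"%, a difference of 30.4 points, with 10% loss. The significance level in Section 3.7 is .05.

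**Assumed, because the article does not give them.** Centre sizes (28/28/27/27, or 50/20/20/20), centre response rates, a two-sided test, 80% power for the sample size, and an unadjusted two-proportion z-test for the efficacy rate.

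**1. The stated sample size.** With mean rate 0.5:
- n = [1.96·√(2·0.5·0.5) + 0.8416·√(0.652·0.348 + 0.348·0.652)]² / 0.304² = (1.386 + 0.567)² / 0.0924 = 41.3 per arm.
- With continuity correction: (41.3/4)·[1 + √(1 + 4/(41.3·0.304))]² = 47.6, so 48 per arm and 96 in total.
- With 10% loss: 96/0.90 = 106.7, so 107, or 108 when rounded per arm. This is within 3% of 110.

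Stratification does not enter this calculation, so N is unaffected by the fix.

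**2. Imbalance within centres, exact 55:55 list.** The number allocated to one arm in a centre is hypergeometric.
- Centre of 28: P(split 19:9 or worse) = 0.048.
- Centre of 27: P(split 18:9 or worse) = 0.075.
- Upper bound for any of the four: 2·0.048 + 2·0.075 = 0.246.
- Simulation, which respects the dependence between centres: about 0.20.

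If the list were drawn by simple randomisation, which the article does not say, the figure would be about 0.36.

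**3. Noise from that imbalance.** Take centre rates of 30, 45, 55 and 70% and no treatment effect.
- The variance of the centre rates over the 110 patients is 0.0212 (0.0214 with divisor 109).
- SD of the arm difference due to centre alone: √(4·0.0214/110) = 0.028, or 2.8 points; its mean is zero.
- P(more than 5 points either way) ≈ 2·[1 − Φ(5/2.79)] = 0.07.
- With centres of 50/20/20/20 the SD is 2.9 points.
- With balanced lists in each centre the SD falls to 0.4 points or less.

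For scale, the ordinary sampling error is √(2·0.25/55) = 0.095, or 9.5 points. The centre part is (2.8/9.5)², about 9% of that variance.

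**4. Type I error.** For the unadjusted test with a single list, simulation (8,000 runs per setting) gave 4.3 to 5.0%, over centre rates from all equal to 20–80% and both sets of centre sizes.

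**5. Power.** Simulated with centre rates of 30–70% and 40,000 runs per setting. The last column is a Mantel-Haenszel test stratified by centre.

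| Centre sizes | True difference | Single list, unadjusted | Single list, centre-adjusted | Stratified list, centre-adjusted |
|---|---|---|---|---|
| 28/28/27/27 | 30.4 points | 89.2% | 92.0% | 92.7% |
| 28/28/27/27 | 20 points | 54.1% | 58.4% | 59.3% |
| 50/20/20/20 | 20 points | 55.0% | 59.7% | 61.2% |

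Most of the gain comes from adjusting for centre, and the stratified list adds a little more. A stratified list without adjustment gains little or nothing, and the test becomes conservative: type I error is about 3.5% in this setting.

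**The case against.** The strongest reply is that the article condenses a fuller protocol. Section 2.5 never says that the list is unstratified, and four centre lists adding to 110 would fit its sentence too. That stands as a caution. Yet the section gives generator, software, ratio, concealment, custodian and timing, and everything in it reads as one trial-wide series. The point therefore concerns the scheme as described. Similarly, a separate analysis plan may add a centre term that Section 3.7 omits.

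A second reply is that the effect is small: about 9% of sampling variance, under centre rates that are assumed. That also stands and sets the size of the point.

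Three stronger readings are tempting, and the documents do not support them.
- A reader might infer that Western care is site-specific. Section 3.1 puts both groups under one national guideline, and Section 4 adds training in standard operating procedures for all staff.
- A reader might infer from Section 2.7 that each hospital grades the outcome in its own way. That section concerns eligibility, judged before randomisation. Section 3.2 scores the efficacy rate from one common table with fixed cut-offs.
- A reader might infer that chance imbalance can pass for a treatment effect. Under valid randomisation it averages zero, and the test's error rate already covers it, as step 4 shows.

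**Conclusion.** The point holds as a cheap improvement in precision. It is not a source of bias or of inflated false positives. As described, the allocation leaves about a 20% chance that some centre splits 2:1 or worse, given centres of 27 or 28 and an exact 55:55 list. If centre response rates spanned 30 to 70%, stratifying and adjusting would gain roughly 4 points of power at the planned difference (89% to 93%) and about 5 to 6 points at a true difference of 20 points. If centres respond alike, there is nothing to gain in power. Both the centre sizes and the centre rates are assumptions, since the article gives neither.

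**What to change.** Generate the SAS list stratified by the four centres, with randomly permuted blocks of varying size that are not disclosed to the sites. Issue a separate, sequentially numbered envelope or kit series to each centre. In Section 3.7, include centre in the between-arm comparison: for example, a Mantel-Haenszel test for the efficacy rate and centre as a factor for continuous outcomes. Make both changes together, because stratifying without adjusting forgoes most of the gain. If the full protocol already stratifies, it is enough to say so in Section 2.5 and add centre to the analysis.

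The cost is a few lines of code and four series instead of one, with N still 110. The one downside is slightly more predictable allocation within blocks, which varying block sizes and central custody of the list limit.

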### Blinding

2.6

The trial has a double-blind design, in which neither the researchers nor the participants will be aware of the subjects’ groups during the trial. The dosage form, color, and smell of the placebo will be similar to JWQYD. In addition, the study team will be instructed not to communicate with participants or their families about the possible grouping of the patients. Only in an emergency (such as a serious adverse event) or when the patient needs to receive emergency treatment will the investigator be required to report it to the main investigator to decide whether to expose the blind.

### Diagnostic criteria

2.7

Participants must meet the Western medicine standard of ARDS diagnosis (Table 1),^[22]^ and the TCM syndrome judgement standard of asthma (Table 2).^[23]^ The determination of syndrome differentiation and treatment in each research center should be independently determined by 2 designated deputy chief TCM physicians.

**Table 1 T1:**
[figure not shown]
Western medicine diagnostic criteria for acute respiratory distress syndrome.

**Table 2 T2:**

Traditional Chinese medicine criteria for syndrome of asthmatic patient.

### Qualification criteria

2.8

#### Inclusion criteria

2.8.1

Patients must meet all the following criteria:

(1)Aged 20 years to70 years(2)Meet the ARDS diagnostic standard(3)Conform to the standard of disease differentiation in TCM(4)In order to conform to the Declaration of Helsinki and Chinese clinical trial research regulations, the patient or family members must know the content of the study and sign informed consent voluntarily.

#### Exclusion criteria

2.8.2

Patients who meet 1 or more of the following exclusion criteria cannot be included:

(1)Pregnant or lactating women(2)Those who are allergic to the drugs used in the program(3)Those with surgical pointer(4)Patients with serious bodily diseases, acquired immune deficiency syndrome, or malignant tumors(5)Patients who may die, refuse active rescue, or are unwilling to receive Western medical treatment within 12 hours after entering the ICU(6)Currently participating in other drug research studies(7)Patients with severe diseases of the liver, kidney, hemopoietic system, or metabolic endocrine system, leading to organ dysfunction.

### Termination and withdrawal criteria

2.9

All participants will be informed that they have the right to withdraw from the trial and if they do, they will also receive the standard treatment. The reason for withdrawal will be recorded in their case report file (CRF). The criteria for discontinuing treatment and withdrawing patients from the study are:

(1)The experience of adverse events related to taking the drugs, and the researchers determine that it is not appropriate to continue administering the drugs(2)Required treatment for another serious disease during the study(3)Poor compliance or withdrawal midway through the study(4)Inability to tolerate 2 weeks of the intervention and cannot continue the research due to the automatic requirement of discharge or transfer(5)Giving up treatment in advance due to economic burden and/or other factors(6)The experience of a serious adverse event in the process of the trial, such as a life-threatening incident or even death, and the researchers could not continue

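### Section 2.9 uses one list for stopping study drug and for leaving the study; this invites outcome-related loss of data and undermines the promised intention-to-treat analysis

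*Protocol article*

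**What the plan says.** Section 2.9 (Termination and withdrawal criteria) gives six criteria under one introduction: "The criteria for discontinuing treatment and withdrawing patients from the study are". Stopping the drug and leaving the study therefore have the same triggers. They include:

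- a drug-related adverse event after which the researchers judge further dosing unsuitable;
- treatment needed for another serious disease;
- "Poor compliance or withdrawal midway through the study";
- "Inability to tolerate 2 weeks of the intervention and cannot continue the research due to the automatic requirement of discharge or transfer";
- giving up treatment for cost or other reasons;
- a serious adverse event, "such as a life-threatening incident or even death, and the researchers could not continue".

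The reason for withdrawal goes into the case report file. The section does not say that a patient who stops the drug continues to be assessed.

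Four other sections bear on this:

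- Section 3.7 (Statistical analyses): "All data analyses will then be based on treatment intention".
- Section 3.5 (Adverse events): any serious adverse event stops the intervention at once. Leaving the study is not mentioned.
- Section 3.2 (Determination of results): 28-day mortality and 1-year all-cause mortality are outcomes. The efficacy rate needs a TCM score after treatment. The readmission rate is divided by patients who completed follow-up.
- Section 3.8 (Ethics and communication): patients are contacted by telephone during follow-up.

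**The concern.** An intention-to-treat analysis needs two things: each patient is analysed in the assigned arm, and outcomes are sought for everyone randomised, on or off the drug. Section 3.7 promises the first. Section 2.9, followed literally, works against the second, because a site that stops the drug for a listed reason may close the patient's record by the same act.

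Most of the listed reasons are not independent of outcome. Toxicity, a new serious illness, non-compliance and death follow from the disease or its treatment, and their frequency can differ between arms. Patients who still have a post-treatment score or blood gas would then be a selected group, and comparing them would no longer be a randomised comparison.

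An analysis plan can specify how missing values are handled. It cannot recover measurements that sites did not take because the protocol told them the patient had left.

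**Working it through.** **Inputs from the article.** Total 110, allocated 1:1, so 55 per arm (sections 2.1 and 2.4). Planning rates 65.2% and 34.8%, and 10% lost during follow-up (section 2.4). Significance at 0.05 (section 3.7). Background mortality from the Introduction: "the mortality rate of ARDS patients is as high as 30% to 40" per cent. Power and sidedness are not stated; I assume two-sided 5% and 80% power.

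**Step 1. The plan's own sample size.** The difference is 0.652 − 0.348 = 0.304 and the mean rate is 0.500.

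- Without continuity correction: n = [1.96·√(2·0.5·0.5) + 0.842·√(0.652·0.348 + 0.348·0.652)]² / 0.304² ≈ 41.3.
- With continuity correction: 48 per arm.
- With 10% loss: 48/0.9 = 53.3, so 54 per arm or 108 in total.

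This is close to the stated 110, so the sample size is not in dispute.

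**Step 2. Patients left if deaths were dropped** (an assumption; the article does not say they are). Power uses the normal approximation without continuity correction and takes the planning rates to hold among those who remain.

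| Loss | Patients left of 110 | Power |
|---|---|---|
| 10% (planned) | 110 × 0.90 = 99 | 87% |
| 30% | 110 × 0.70 = 77 | 77% |
| 40% | 110 × 0.60 = 66 | 70% |

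**Step 3. Bias if deaths were dropped and differed by arm** (assumed figures). Suppose 35% of all randomised patients respond in both arms, so there is no true difference.

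- Arm with 40% deaths: 0.35/0.60 = 58.3% of survivors.
- Arm with 30% deaths: 0.35/0.70 = 50.0% of survivors.

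The arm with more deaths appears better by 8.3 points. The direction depends only on which arm has more deaths.

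**Step 4. The same mechanism at the planning rates.** Take 65.2% and 34.8% as rates among survivors and assume deaths of 30% with JWQYD and 20% with placebo.

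- Survivors only: 65.2 − 34.8 = 30.4 points.
- All randomised, death as not effective: 0.652 × 0.70 = 45.6% and 0.348 × 0.80 = 27.8%, a difference of 17.8 points.

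Dropping deaths would overstate the difference by 12.6 points in this example, without changing its sign.

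**Step 5. The sections side by side.** Section 2.9 ties a serious adverse event to leaving the study when the researchers could not continue. Section 3.5 ties any serious adverse event to stopping the drug and is silent on the study. Section 3.7 requires analysis by intention to treat. Section 3.2 nevertheless uses completers as the denominator for readmission. A site cannot tell from these sections whether a patient taken off the drug should still be assessed.

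**The case against.** A reader might infer that the intention-to-treat analysis cannot be done at all. The article does not support that. It nowhere excludes withdrawn patients from analysis and nowhere says that their later data go uncollected. The only explicit completers' denominator is the one for readmission.

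A reader might also take section 2.9 to remove everyone with a serious adverse event or an early discharge. It does not. The discharge criterion requires inability to tolerate the two weeks and that the patient "cannot continue the research due to the automatic requirement of discharge or transfer". The serious-event criterion applies when the researchers could not continue. Section 3.5 already speaks of stopping the intervention only.

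Nor are deaths lost from the mortality comparison. Section 3.2 counts deaths from the start of the trial to day 28, and a patient who dies has supplied that endpoint.

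The magnitude has limits too. The 30% to 40% is a general figure for ARDS with no stated time horizon. Sections 2.8.1 and 2.8.2 restrict age to 20 to 70 and exclude malignancy, severe organ dysfunction and patients who may die within 12 hours of entering the ICU, so this trial's mortality may differ. The 10% allowance is for loss during follow-up, and deaths count against it only if they are treated as losses. One can construct a reversal of sign: with 65% and 60% response among survivors and 30% and 20% deaths, +5 points becomes 45.5% − 48.0% = −2.5 points. That result depends on a 60% control rate which the article does not use.

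Finally, this is a condensed article, and rules for missing data may stand in a full protocol or analysis plan.

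All of this narrows the point. What remains is a rule that the article does state: one list for two acts, with outcome-related triggers. Two triggers carry a qualifier about being unable to continue in the research, but what that means is undefined; poor compliance, another serious disease and giving up treatment carry none.

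**Conclusion.** The point holds in a limited form. Section 2.9 merges stopping the drug with leaving the study, and nothing in the article keeps the affected patients in follow-up. As written, the rule invites informative loss of data and weakens the intention-to-treat analysis without ruling it out. The outcomes most exposed are the efficacy rate, PaO2/FiO2, lung water, and the later vital status and readmission of patients who leave early. Observed deaths remain valid in 28-day mortality.

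The size and direction of the bias cannot be determined from the article. The retained numbers of 77 to 66 and the distortions of 8.3 and 12.6 points all rest on two assumptions: that deaths would be dropped, and that mortality takes the values used. They show what is possible and do not predict the result. The wording should still be corrected, because the change is cheap and uncollected outcomes may not be recoverable.

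**What to change.** Reconcile sections 2.9, 3.5 and 3.7 by splitting section 2.9 in two.

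1. **Stopping study drug.** Keep the sponsor's existing reasons. Sections 2.9 and 3.5 differ on what follows a serious adverse event, and the sponsor must make them agree; I take no view on which rule is right.
2. **Leaving the study.** Limit this to withdrawal of consent for further data. Remove death from the list, since it is an outcome.

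Then state that:

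- every randomised patient, on or off the drug and in or out of hospital, is followed for 28-day vital status and the 1-year telephone contact;
- day-14 measurements are taken wherever the patient is still in hospital;
- all patients are analysed in the assigned arm;
- the denominator of the efficacy rate is all randomised patients, and those who die before the post-treatment assessment count as not effective.

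**Cost.** Wording, a site instruction and some extra telephone calls, for which section 3.8 already provides the route. Telephone contact cannot supply blood gases, lung water or a full score, so these will still be missing for some patients who left hospital early.

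The change does not itself alter the total of 110. The sponsor should, however, confirm whether the planning rates already count deaths as failures. If they are rates among survivors, then with equal mortality of 30% to 40% in both arms the all-randomised rates are 45.6% v 24.4% to 39.1% v 20.9%. Power at 55 per arm is then about 65% to 55% (same approximation as in step 2).
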